## 12. DISCONTINUATION OF VACCINATIONS AND/OR WITHDRAWAL FROM STUDY

### 12.1 Discontinuation of Vaccinations

Any discontinuation or planned discontinuation from further vaccinations will be discussed with the Sponsor. Volunteers will be discontinued from further vaccination for any of the following reasons:

1. Pregnancy
2. Intercurrent HIV Infection
3. Use of systemic corticosteroids, immunosuppressive, antiviral, anticancer, anti-tuberculosis or other medications considered significant by the investigator. Note: Volunteers requiring chronic corticosteroids (> 2 weeks) or long term therapy will not receive any further vaccinations.
4. A disease or condition or an adverse event that may develop, regardless of relationship to the Investigational Product, if the Principal Investigator or designee is of the opinion that further study vaccinations will jeopardize the safety of the volunteer
5. Anaphylaxis, bronchospasm, laryngeal oedema, convulsions or encephalopathy following study vaccinations
6. Life-threatening adverse event following study vaccination unless not related to the Investigational Product and fully resolved

7. Any immediate hypersensitivity reaction judged to be related to the Investigational Product, if the Principal Investigator or designee is of the opinion that further study vaccinations will jeopardize the safety of the volunteer
8. Volunteer's request to discontinue further vaccination

The following are parameters that require resolution and/or review of clinical history by the Principal Investigator or designee and consultation with the Medical Monitor, prior to continuation of study vaccination(s):

1. Any of the following abnormal laboratory parameters that are known at the time of vaccination:

*Haematology*

- Haemoglobin  $\leq 9.0$  g/dL **or**  $\leq 5.55$  mmol/L
- Absolute Neutrophil Count (ANC):  $\leq 1000/\text{mm}^3$  **or**  $\leq 1.0 \times 10^9/\text{L}$
- Absolute Lymphocyte Count (ALC):  $\leq 500/\text{mm}^3$  **or**  $\leq 0.5 \times 10^9/\text{L}$
- Platelets:  $\leq 90,000 \geq 550,000/\text{mm}^3$  **or**  $\leq 90 \times 10^9 \geq 550 \times 10^9/\text{L}$

*Chemistry*

- Creatinine:  $>1.4 \times \text{ULN}$
- AST:  $\geq 2.6 \times \text{ULN}$
- ALT:  $\geq 2.6 \times \text{ULN}$

2. Receipt of inactivated/killed/subunit vaccines (non-HIV) or immunoglobulin within the previous 14 days or planned receipt within 14 days after vaccination with Investigational Product

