3. Receipt of live attenuated vaccines within the previous 60 days or planned receipt within 60 days after vaccination with Investigational Product
4. A Grade 3 or 4 local reactogenicity involving the major part of the injected arm circumference
5. If the use of a short tapering course ( $<2$  weeks) of corticosteroids is required, the study vaccinations may be continued after a 4-week washout period, provided that the medical condition requiring this therapy has completely resolved and in the opinion of both the site investigator and Medical Monitor, the continuation of the study vaccinations will not jeopardize the safety of the volunteer.

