### **17.3 Criteria for Pausing the Study**

Enrolment and vaccinations will be stopped and a safety review conducted by the SRB for any of the following criteria:

- one subject experiences an SAE that is probably or definitely related to the investigational vaccine(s), or two or more subjects experience similar SAEs which are possibly related to the investigational vaccine(s);
- there is a subject death assessed as possibly, probably or definitely related to the investigational vaccine(s)
- one subject experiences injection site ulceration, sterile abscess or necrosis associated with vaccine administration; or
- one subject experiences a severe allergic reaction, such as laryngospasm, bronchospasm or anaphylaxis, associated with vaccine administration.

The Sponsor will request a review by the SRB, or the SRB chair if other SRB members cannot be convened, to be held within 2 business days of the Sponsor learning of the event. The individual volunteer(s)/or study may be unblinded at the discretion of the SRB.

Following this review, the SRB will make a recommendation regarding the continuation or suspension of the vaccinations or the trial and communicate this decision immediately to the Sponsor. The Sponsor then will inform the Principal Investigators without delay.

Additional *ad hoc* review may be specifically requested by the Sponsor, the Principal Investigator(s) or by the SRB.

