| Infection (any other than HIV infection)                                                    | Localized, no systemic antimicrobial treatment indicated AND Symptoms causing no or minimal interference with usual social & functional activities | Systemic antimicrobial treatment indicated OR Symptoms causing greater than minimal interference with usual social & functional activities  | Systemic antimicrobial treatment indicated AND Symptoms causing inability to perform usual social & functional activities OR Operative intervention (other than simple incision and drainage) indicated | Life-threatening consequences (e.g., septic shock)                                                                                                                     |
| INJECTION SITE REACTIONS                                                             |                                                                                                                                                    |                                                                                                                                             |                                                                                                                                                                                                         |                                                                                                                                                                        |
| Injection site pain (pain without touching)
Or
Tenderness (pain when area is touched) | Pain/tenderness causing no or minimal limitation of use of limb                                                                                    | Pain/tenderness limiting use of limb OR Pain/tenderness causing greater than minimal interference with usual social & functional activities | Pain/tenderness causing inability to perform usual social & functional activities                                                                                                                       | Pain/tenderness causing inability to perform basic self-care function OR Hospitalization (other than emergency room visit) indicated for management of pain/tenderness |

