| Injection site reaction (localized)                                                         |                                                                                                                                                    |                                                                                                                                             |                                                                                                                                                                                                         |                                                                                                                                                                        |
| Adult > 15 years                                                                  | Erythema OR Induration of 5x5 cm – 9x9 cm (or 25 cm  – 81cm  )                                                             | Erythema OR Induration OR Edema > 9 cm any diameter (or > 81 cm  )                                                              | Ulceration OR Secondary infection OR Phlebitis OR Sterile abscess OR Drainage                                                                                                                           | Necrosis (involving dermis and deeper tissue)                                                                                                                          |
| Pediatric ≤ 15 years                                                                 | Erythema OR Induration OR Edema present but ≤ 2.5 cm diameter                                                                                      | Erythema OR Induration OR Edema > 2.5 cm diameter but < 50% surface area of the extremity segment (e.g., upper arm/thigh)                   | Erythema OR Induration OR Edema involving ≥ 50% surface area of the extremity segment (e.g., upper arm/thigh) OR Ulceration OR Secondary infection OR Phlebitis OR Sterile abscess OR Drainage          | Necrosis (involving dermis and deeper tissue)                                                                                                                          |

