| Platelets, decreased                                                                                                                                                                                                                                                                                                                                                                               | 100,000 – 124,999/mm 
100.000 x 10^9 – 124.999 x 10^9/L                  | 50,000 – 99,999/mm 
50.000 x 10^9 – 99.999 x 10^9/L                    | 25,000 – 49,999/mm 
25.000 x 10^9 – 49.999 x 10^9/L           | < 25,000/mm 
< 25.000 x 10^9/L |
| WBC, decreased                                                                                                                                                                                                                                                                                                                                                                                     | 2,000 – 2,500/mm 
2.000 x 10^9 – 2.500 x 10^9/L                          | 1,500 – 1,999/mm 
1.500 x 10^9 – 1.999 x 10^9/L                        | 1,000 – 1,499/mm 
1.000 x 10^9 – 1.499 x 10^9/L               | < 1,000/mm 
< 1.000 x 10^9/L   |

| LABORATORY                                                                                                                                                                                                                                                    |                                                           |                                         |                                                |                                             |
|---------------------------------------------------------------------------------------------------------------------------------------------------------------------------------------------------------------------------------------------------------------|-----------------------------------------------------------|-----------------------------------------|------------------------------------------------|---------------------------------------------|

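### Section 12.1 item 4 ties an extent condition to Grade 3-4, but in the adult row of Appendix C extent alone never takes swelling or erythema past Grade 2

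*Protocol*

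**What the plan says.** The second list in Protocol Section 12.1 names findings that need resolution and/or review by the investigator, together with Medical Monitor consultation, before vaccination continues. Item 4 is the only one about a local reaction: "A Grade 3 or 4 local reactogenicity involving the major part of the injected arm circumference". Both conditions, grade and extent, must hold.

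Section 9.1.1 sends the grading of local reactions to Appendix C, as a guideline. The relevant entries are:

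- **Localized injection site reaction, adults over 15 years.** Grade 1 is erythema or induration from 5x5 to 9x9 cm. Grade 2 is "Erythema OR Induration OR Edema > 9 cm any diameter", with no upper limit. Grade 3 is "Ulceration OR Secondary infection OR Phlebitis OR Sterile abscess OR Drainage". Grade 4 is necrosis.
- **The same reaction, age 15 or under.** Grade 3 includes "Erythema OR Induration OR Edema involving ≥ 50% surface area of the extremity segment".
- **Injection site pain or tenderness.** Grade 3 is "Pain/tenderness causing inability to perform usual social & functional activities".

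Section 10.2 leaves the final severity grade to the site's Principal Investigator, on functional criteria. Appendix C adds that a clinical event which could fall under either of two grades takes the higher one. Section 17.3 separately pauses the whole study if "one subject experiences injection site ulceration, sterile abscess or necrosis associated with vaccine administration".

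**The concern.** Item 4 describes its target by how much of the arm is involved. In this population, however, extent plays no part in reaching the grade that item 4 also demands. A large but uncomplicated and non-disabling reaction, which the extent wording brings to mind first, fails the grade condition.

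What is at stake is one decision: whether a volunteer with swelling or erythema over most of the arm is dosed again without a required conversation with the Medical Monitor. Section 3.2 says no safety data for HIV-MAG are available yet. Groups 1-3 receive electroporated injections into both deltoids at months 0, 1 and 2, so the decision could arise.

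**Working it through.** No figure in the plan needs reproducing. The check sets the trigger beside the grading table and then looks at every other route to the same consultation.

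**1. Which row applies.** Section 5.2.3 requires age 18 or over at screening, with the 51st birthday not reached at first vaccination. The adult row covers everyone; the row with an extent-based Grade 3 covers no one.

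**2. Can extent alone meet item 4?** No. Above 9 cm the adult row gives Grade 2 without limit. Its Grade 3 and 4 entries are complications with no size criterion.

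**3. Does a reaction over most of the arm exceed 9 cm?** Take the major part to mean more than half of the circumference C. Then extent > C/2, which is above 9 cm whenever C is at least 2 x 9 = 18 cm. For an assumed adult range of C = 22 to 40 cm (not in the protocol), C/2 = 11 to 20 cm. Such reactions are all Grade 2 on size, and none is Grade 3.

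**4. Routes by which item 4 can still be met.**

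- Grade 3-4 pain or tenderness, at least severe enough to prevent usual activities.
- A listed complication: 5 at Grade 3 plus necrosis at Grade 4 makes 6. Three of these (ulceration, sterile abscess, necrosis) already pause the study under Section 17.3 when associated with vaccination. That leaves 6 - 3 = 3: secondary infection, phlebitis and drainage.
- An investigator grade that departs from the guideline, or the higher-grade rule where functional impact is borderline. The functional criteria themselves do not grade on extent.

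**5. Other controls.**

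| Control | Section | Mandatory consultation before that volunteer's next dose? |
|---|---|---|
| Site examination before each dose | 6.2 | No |
| Clinic visits on days 3, 7 and 14 | 6.3 | No |
| Investigator may stop vaccination on own opinion | 12.1, first list, item 4 | No; sponsor discussion is required only if discontinuation is made or planned |
| Weekly Protocol Safety Review Team review, chaired by a Medical Monitor | 17.1 | No |
| Study pause | 17.3 | Does not cover uncomplicated swelling or erythema |

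**6. Laboratory entries in the same list, for comparison.**

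| Parameter | Consultation threshold | Appendix C Grade 2 | Part of Grade 2 caught |
|---|---|---|---|
| AST, ALT | at least 2.6 x ULN | 2.6-5.0 x ULN | All |
| Neutrophils | 1000/mm³ or less | 750-999/mm³ | All |
| Creatinine | above 1.4 x ULN | 1.4-1.8 x ULN | All but the lowest value |
| Platelets (low) | 90,000/mm³ or less | "50,000 – 99,999/mm"³ | Most |
| Haemoglobin | 9.0 g/dL or less | 9.0-9.9 g/dL | Lowest value only |
| Lymphocytes | 500/mm³ or less | 500-599/mm³ | Lowest value only |

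The comparison is mixed: haemoglobin and lymphocytes in effect start at Grade 3.

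**7. Doses to which item 4 can apply, if all 75 volunteers complete.** Groups 1-3: 45 x 3 = 135 (months 1, 2 and 6). Groups 4-5: 30 x 1 = 30 (month 4). Total 165, of which vaccine recipients account for 36 x 3 + 24 x 1 = 132 and placebo recipients for 9 x 3 + 6 x 1 = 33. Only 45 x 2 = 90 repeat the preceding product, and 9 x 2 = 18 of those are placebo; the other 45 + 30 = 75 follow a product switch.

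**The case against.** The strongest reply is that item 4 is a deliberate severity-plus-extent threshold. It can be met, it contradicts nothing, and what it leaves out is a reaction the protocol's own scale calls moderate. On that view, moving the trigger down a grade is a preference. It stands that item 4 is workable. A reader might infer that item 4 is inoperative or conflicts with Appendix C; the documents do not support that, because the pain, complication and investigator-judgement routes remain open. The reply does not explain why a rule worded by extent should miss nearly all reactions that are notable only for extent.

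Four further points stand in whole or part:

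- **Mitigation is real.** Doses are nominally at least 28 days apart, so about 28/7 = 4 weekly team reviews fall between consecutive doses, with a Medical Monitor in the chair and each site's investigator or designee a member. Section 13.2 asks for prompt data entry. This lowers the risk without creating a condition for the individual's next dose.
- **The laboratory comparison is only supporting.** A reader might infer that the rest of the list always acts from Grade 2. Haemoglobin and lymphocytes show otherwise. The laboratory cut-offs also repeat those of exclusion criterion 9, so they look like a re-check of current fitness rather than a Grade 2 policy.
- **The proposed wording leaves an uneven order.** Grade 2 redness over most of the arm would require consultation, while Grade 3 phlebitis of limited extent would not. The latter is the protocol's existing choice and is left alone.
- **The Study Operations Manual is not at hand.** Section 17.1 allows it to specify further ad hoc team reviews, so an operational gap cannot be established from the protocol alone.

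**Conclusion.** The mismatch between Section 12.1 item 4 and the adult row of Appendix C is there on the text. Followed as written, uncomplicated and non-disabling swelling or erythema over most of the arm stays at Grade 2 and does not make Medical Monitor consultation mandatory before the next dose. The exceptions are an investigator who grades outside the table or applies the higher-grade rule to borderline functional impact.

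The point is minor. The existing controls keep the harm small, and the primary endpoints, which count moderate or greater reactions, are unaffected. A reader might take 165 as the number of doses at risk. It is only the ceiling on where the rule can apply; the protocol gives no rate of extensive reactions, so the number affected cannot be estimated. Nor is every local reaction Grade 2 whatever its size: erythema or induration of 5x5 to 9x9 cm is Grade 1, and the cap matters only above 9 cm.

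The conclusion assumes that the major part means more than half of the circumference, that adult arms measure at least 18 cm round, and that the Study Operations Manual adds no trigger of its own.

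**What to change.** In Section 12.1 item 4, insert after the mention of Grade 3 or 4 local reactogenicity the phrase *or erythema, swelling or induration of Grade 2 or higher*, with the existing extent condition applying to both parts. By the size check, the Grade 2 floor excludes no reaction over most of an adult arm. Appendix C and the endpoints stay as they are.

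The cost is one line of text, with no extra data, visits or volunteers. The downside is a number of additional Medical Monitor consultations that is likely small but cannot be quantified from the protocol. Grade 3-4 reactions of limited extent are still not brought in.

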## **12.2. Follow-Up after Discontinuation of Further Vaccinations**

Volunteers who have study vaccinations discontinued due to adverse events will be followed until the adverse event resolves or stabilizes or up to the end of the study, whichever comes last. These volunteers will not be replaced.

## **12.3 Withdrawal from the Study (Early Termination)**

Volunteers may be withdrawn from the study permanently for the following reasons:

1. Volunteers may withdraw from the study at any time if they wish, for any reason
2. The Principal Investigator or designee has reason to believe that the volunteer is not complying with the protocol
3. If the Sponsor decides to terminate or suspend the study
4. If a volunteer becomes infected with HIV (through exposure in the community)

If a volunteer withdraws or is withdrawn from the study, all termination visit procedures will be performed according to the Schedule of Procedures (Appendices A-B) where possible. Every effort will be made to determine and document the reason for withdrawal.

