## 5.0 STUDY ENDPOINTS AND STUDY DESIGN

### 5.1 Study Endpoints

#### 5.1.1 Primary Endpoints

##### *Safety and tolerability:*

To assess safety and tolerability of the different prime-boost regimens:

1. Proportion of volunteers with moderate or greater reactogenicity (i.e., solicited adverse events) during a 7 day follow-up period after each vaccination
2. Proportion of volunteers with moderate or greater and/or vaccine-related unsolicited adverse events (AEs) including safety laboratory (biochemical, haematological) parameters, from the day of each vaccination up to 28 days post each vaccination.
3. Proportion of volunteers with vaccine related serious adverse events (SAEs) collected throughout the study period

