## **6.6 Final Study Visit or Early Termination Visit**

Assessments and procedures will be performed according to the Schedule of Procedures (Appendices A-B).

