#### **9.1.4 Other adverse events**

Other adverse events (AEs) will be collected through one month after the last vaccination in all groups. Serious Adverse Events (SAEs) will be collected throughout the entire study period. Open ended questions will be asked at time points according to the Schedule of Procedures (Appendices A-B). All adverse events will be graded using Appendix C, Adverse Event Severity Assessment Table, as a guideline and will be assessed for causality to the IP.

For more information regarding adverse events refer to Section 10.0, Adverse Events.

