#### **9.1.5 Concomitant Medications**

During the study, information regarding concomitant medications and reasons for their use will be solicited from the study volunteers at each visit and recorded.

Concomitant receipt of Investigational Products, including other HIV vaccines, is prohibited during the study.

If clinically indicated, inactivated/killed/subunit vaccines (non-HIV) and immunoglobulin may be given up to 14 days before study vaccination(s) or 14 days after the most recent study vaccination (following the post-vaccination blood draw). Live-attenuated vaccines may be given 60 days before study vaccination(s) or 60 days after the most recent post-vaccination blood draw. However, the study vaccination(s) should not be given if there are any continuing symptoms from recently administered non-study vaccines. In this situation, the site investigator should consult with the Medical Monitor before administering the next study vaccination.

If the use of a short tapering course (<2 weeks) of oral corticosteroids is required, the study vaccinations may be continued after a 4-week washout period provided that the medical condition requiring this therapy has completely resolved and in the opinion of both, the site investigator and Medical Monitor, the continuation of the study vaccinations will not jeopardize the safety of the volunteer. Volunteers requiring chronic (> 2 weeks) or long term therapy will not receive any further vaccinations but will continue with follow-up visits until the end of the study.

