| Local and Systemic Reactogenicity      |        | X  | X   | X   |     | X  | X   | X   |     | X  | X   | X   |     |     |      | X  | X    | X    |      |      |                |                        |

| Study Month                                                                                   |        | M0  |     |     |     | M1  |     |     |     | M2  |     |     |     | M3             | M5   | M6   |      |      |      | M7             | M9   | M12                    |
|-----------------------------------------------------------------------------------------------|--------|-----|-----|-----|-----|-----|-----|-----|-----|-----|-----|-----|-----|----------------|------|------|------|------|------|----------------|------|------------------------|
| Week                                                                                          |        | W0  |     | W1  | W2  | W4  |     |     |     | W8  |     | W9  | W10 | W12            | W20  | W24  |      | W25  | W26  | W28            | W36  | W48 or ET  |
| Study Day                                                                                     | Screen | 0   | D3  | D7  | D14 | D28 | D31 | D35 | D42 | D56 | D59 | D63 | D70 | D84            | D140 | D168 | D171 | D175 | D182 | D196           | D252 | D336                   |
| Visit Windows (Days)                                                                          |        | -42 | ± 1 | ± 3 | ± 3 | ± 3 | ± 1 | ± 3 | ± 3 | ± 3 | ± 1 | ± 3 | ± 3 | ± 3            | ± 3  | ± 7  | ± 1  | ± 3  | ± 3  | ± 3            | ± 7  | ± 7                    |
|                                                                                               |        |     |     |     |     |     |     |     |     |     |     |     |     |                |      |      |      |      |      |                |      |                        |
| Adverse Events                                                                                |        | X   | X   | X   | X   | X   | X   | X   | X   | X   | X   | X   | X   | X              | X    | X    | X    | X    | X    | X              |      |                        |
| Serious Adverse Events                                                                        | X      | X   | X   | X   | X   | X   | X   | X   | X   | X   | X   | X   | X   | X              | X    | X    | X    | X    | X    | X              | X    | X                      |

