| Cumulative blood volume                                                                       |        | 112 |     |     |     | 121 |     |     | 201 | 299 |     |     | 379 | 482            |      | 580  |      | 610  | 708  | 811            | 909  | 1012                   |

 Early Termination At baseline and at least 30 min post vaccination If HIV infected, conduct ET visit and request consent for Protocol H. If ET and Protocol H visit occur on same day, do not collect PBMCs for ET visit. Performed to capture SAEs

## APPENDIX B: SCHEDULE OF PROCEDURES GROUPS 4 AND 5

| Study Month                             |        | M0             |     |     |     | M1  | M4             |      |      |      | M5   | M7             | M10            | M12                    |
|-----------------------------------------|--------|----------------|-----|-----|-----|-----|----------------|------|------|------|------|----------------|----------------|------------------------|
| Week                                    |        | W0             |     | W1  | W2  | W4  | W16            |      | W17  | W18  | W20  | W28            | W40            | W48 or ET  |
| Study Day                               | Screen | 0              | D3  | D7  | D14 | D28 | D112           | D115 | D119 | D126 | D140 | D196           | D280           | D336                   |
| Visit Windows (Days)                    |        | -42            | ± 1 | ± 3 | ± 3 | ± 3 | ± 3            | ± 3  | ± 3  | ± 3  | ± 3  | ± 7            | ± 7            | ± 7                    |
| Investigational Product          |        |                |     |     |     |     |                |      |      |      |      |                |                |                        |
| HIV-MAG + GENEVAX® IL12 / Placebo       |        | X  |     |     |     |     | X  |      |      |      |      |                |                |                        |
| Ad35-GRIN/ENV / Placebo                 |        | X  |     |     |     |     | X  |      |      |      |      |                |                |                        |
| Consent /Assessments/Counselling |        |                |     |     |     |     |                |      |      |      |      |                |                |                        |

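### The Early Termination column schedules no adverse event, reactogenicity or medication check, so clinical events may go unrecorded for a volunteer who exits soon after a vaccination

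*Protocol*

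**What the plan says.** Protocol section 12.3 covers volunteers who withdraw or are withdrawn: "all termination visit procedures will be performed according to the Schedule of Procedures (Appendices A-B) where possible". Section 6.6, on the final or early termination (ET) visit, lists no procedures of its own and points to the same appendices.

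Neither appendix gives ET its own column. It shares the last one, headed W48 or ET, with the Month 12 visit at D336. In that column, in both appendices:

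- the rows "Adverse Events", "Local and Systemic Reactogenicity" and Concomitant Medications are blank;
- Serious Adverse Events is marked, as are general physical examination, vital signs, lymph nodes, haematology, chemistry, CD4/CD8, urinalysis, the HIV test and, for women, the pregnancy test;
- interim medical history is marked, with the footnote "Performed to capture SAEs" (footnote 4 in Appendix A, footnote 6 in Appendix B).

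No footnote alters the column for someone recently vaccinated.

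The text asks for more. Section 9.1.4: "Other adverse events (AEs) will be collected through one month after the last vaccination in all groups", although it also times the open-ended questions by the Schedule. Section 9.1.5: "information regarding concomitant medications and reasons for their use will be solicited from the study volunteers at each visit and recorded". In section 5.1.1, primary endpoint 1 counts volunteers with moderate or greater solicited events in the 7 days after each vaccination. Endpoint 2 counts those with moderate or greater and/or vaccine-related unsolicited events, including safety laboratory findings, "from the day of each vaccination up to 28 days post each vaccination".

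**The concern.** The shared column is built for a completer, whose last vaccination was 336 - 168 = 168 days earlier (Groups 1-3) or 336 - 112 = 224 days earlier (Groups 4-5). By then both endpoint windows have long closed, and asking only about SAEs is reasonable. The same column also applies to a volunteer who leaves a few days or weeks after a dose, while a window is open.

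A site that follows the column does not ask that volunteer about non-serious events since the last visit. A site that asks, as sections 9.1.4 and 9.1.5 suggest, departs from the Schedule. The primary endpoints are safety proportions in groups of 12 vaccinees and 3 placebo recipients, so single volunteers matter. The analysis plan can choose how to treat missing data, but it cannot recover answers to questions that were never put.

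**Working it through.** **1. Cell check.** Each row was read against the day headers of both appendices.

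| Row | Last mark, Appendix A | Last mark, Appendix B | At W48 or ET |
|---|---|---|---|
| Adverse Events | D196 | D140 | blank in both |
| Local and Systemic Reactogenicity | D175 | D119 | blank in both |
| Concomitant Medications | D196 | D140 | blank in both |
| Serious Adverse Events | D336 | D336 | marked in both |
| Haematology | D336 | D336 | marked in both |

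**2. Does another provision fill the gap?**

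- The Memory Aid is not kept as a source document (section 9.1). Staff transfer its content by going through it with the volunteer after vaccination (section 6.3), and the ET column schedules no such step.
- Section 10.5 follows events already known. It does not elicit new ones.
- Section 6.5, on unscheduled visits, names no adverse event procedure.
- Section 11.3.2 covers only HIV infection confirmed in a reactogenicity period, and leaves that to case-by-case discussion with the medical monitor.

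None of these schedules the missing questions.

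**3. Exposure, as an upper bound.** Groups 1-3 have four vaccinations and Groups 4-5 have two, over 336 days.

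- Groups 1-3: 4 x 28 = 112 days; 112/336 = 33.3%.
- Groups 4-5: 2 x 28 = 56 days; 56/336 = 16.7%.

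These shares treat every day of a window as exposed. Only events since the last scheduled visit can be missed, so the true exposure is lower. For endpoint 1, only exits before the day-7 visit matter.

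**4. Size per volunteer.** Suppose w volunteers exit inside a window and are counted as event-free. The observed proportion then falls by at most w/N, and on average by w x p/N if exits are unrelated to events with rate p. The protocol gives no dropout rate, so w and p are assumptions.

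- N = 12 vaccinees, w = 1: maximum 1/12 = 8.3 points. With p = 20%, the expected fall is 0.20/12 = 1.7 points.
- N = 12, w = 2 or 3: maximum 16.7 or 25.0 points.
- N = 60 pooled vaccinees, w = 1, 2 or 3: maximum 1.7, 3.3 or 5.0 points.

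**5. Effect on the plan's own figures.** No stated figure addresses this point, but two in section 14.3 presume complete ascertainment.

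- The zero-event upper limit is 1 - 0.025^(1/n): 0.0596 for n = 60 and 0.2646 for n = 12, matching the stated 0.06 and 0.265. If such volunteers were dropped from the denominator instead, it would become 0.285 for n = 11 and 0.063 for n = 57.
- The power example (60 against 15, 36% against 5%, one-tailed Fisher, alpha 5%) reproduces at 0.794 by exact enumeration. If w of the 60 vaccinees have any event lost, the effective rate is 0.36 x (60 - w)/60. Power is then 0.778 (w = 1), 0.744 (w = 3) and 0.688 (w = 6).

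**The case against.** Several points on the other side are sound.

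- A reader might infer that the ET column collects only SAEs. It does not. Examination and safety laboratory tests are marked, and endpoint 2 expressly includes laboratory parameters, so that part is captured at exit.
- Visits 3, 7 and 14 days after each vaccination already record earlier events. Someone who leaves on Day 20 has lost no reactogenicity data, because that window closed at Day 7.
- A volunteer with an earlier qualifying event is already counted, so a later missed event changes nothing.
- The medication mismatch is not special to ET. Those cells are blank for completers too, at D252 and D336 in Appendix A and at D196, D280 and D336 in Appendix B. Medications are also not part of endpoints 1 and 2.
- Stopping vaccination is separate from leaving the study. A volunteer may simply ask to stop (section 12.1), and those stopped for an adverse event stay under follow-up (section 12.2).

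The strongest argument is that someone who exits inside the window of a due visit would also receive that visit's checks. With windows of D3 ±1, D7 ±3, D14 ±3 and D28 ±3, Days 2-17 and 25-28 would be covered. Only Day 1 and Days 18-24 stay open, 8 days per dose: 4 x 8/336 = 9.5% in Groups 1-3 and 2 x 8/336 = 4.8% in Groups 4-5. The protocol does not say this, however, and even this reading leaves Days 18-24 uncovered.

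The Study Operations Manual, which is not at hand, may add detail. It would not remove the conflict within the protocol.

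**Conclusion.** The point holds in conditional form. Followed as written, the ET column omits non-serious adverse events, reactogenicity and medications. For an exit inside an open window, that conflicts with sections 9.1.4 and 9.1.5 and with the endpoint windows. Clinical events since the last scheduled visit may then go unrecorded.

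The documents do not support saying that primary endpoints 1 and 2 are under-counted. That would need three things together: an exit inside a window, a first qualifying event since the last visit, and the volunteer counted as event-free. The protocol gives no dropout rate and does not fix that counting rule, which may sit in the analysis plan.

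A reader might also infer that withdrawals cluster after doses because of how the dose felt, or that Groups 1-3 lose twice as many events as Groups 4-5. No passage documents such clustering, and the 33% and 17% shares bound exposure time, not lost events.

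The effect is probably small. The 8.3 points is a maximum per such volunteer in one group of 12 vaccinees. It remains worth correcting because the omission cannot be repaired at analysis.

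**What to change.** Add a footnote to the W48 or ET column in Appendices A and B, or give ET its own column, so that:

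- an ET visit within 28 days of the last vaccination includes Adverse Events and Concomitant Medications;
- an ET visit within 7 days of it also includes Local and Systemic Reactogenicity;
- in those cases the ET interim history is not limited to SAEs.

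A footnote is enough; splitting the column is a matter of layout. The cost is the footnote and a case report form page for ET, with no added visit or sample.
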